### Confounders and explanatory variables

Maternal and infant characteristics as recorded on the birth registries and perinatal data collections, will be incorporated in the models as potential confounders of vaccine effects on atopic disease (i.e. as common causes of the exposure and the outcomes of interest), or as prognostically important covariates. Both will be selected *a priori* based on causal considerations and the *modified disjunctive cause criterion* proposed by VanderWeele [27]. aided by graphical models of asthma generated in GeNIe modeler [28], and other atopic diseases (see Estcourt et al [19]). Briefly, these will be restricted to:

common causes of the exposure and outcome;the proxies of unmeasured confounders; andthose related to the outcome, but not to the exposure.

The proposed set was measured before the administration of the first dose of wP/aP. Collider stratification bias will be avoided by not including variables in the causal pathway from the exposure to the outcome (i.e. those that occur post exposure).

## Statistical analysis plan

The study population characteristics will be described by state of birth and presented using appropriate summary statistics (means and standard deviations for symmetric continuous distributions, medians and interquartile range for asymmetric distributions, and frequency and proportion for categorical and binary variables). Through the cohort flowchart we will summarise the number and proportion of children that met each of the exclusion criteria. We will also provide a summary of the variables listed in Table 2, overall and by type of vaccine received for dose one.

**Table 2 pone.0260388.t002:** Variables that will be included in the description of the cohort.

Variable	Classification	Description
Child characteristics		
Sex^a^	Dichotomous	Female or male
Gestational age at delivery^a^	An integer measured in weeks	
Method of delivery^a^	Categorical	Vaginal, caesarean or instrumental
Apgar score (5 minutes)	Categorical	< 7, 7, 8, 9, 10
Birthweight	An integer measured in grams	
Aboriginal status^a^	Dichotomous	Aboriginal and/or Torres Strait Islander or non-Aboriginal
Season of birth^a^	Categorical	Summer, autumn, winter, spring
Age at the first dose of pertussis-containing vaccine^b^	An integer measured in days	
Age at first admission to hospital for the above-specified outcomes	An integer measured in months or years	
Number of recurrent events for each outcome of interest	An integer	
Parental factors		
Maternal age	An integer measured in years	
Number of previous pregnancies greater than 20 weeks gestation^a^	Categorical	0, 1, 2 ≥ 3
Maternal smoking during pregnancy^a^	Dichotomous	Yes or no
Mother born overseas	Dichotomous	Yes or no
Paternal age	An integer measured in years	
Index of Relative Socio-economic Advantage and Disadvantage^a^	Categorical	0 to 10% or most disadvantaged, 11 to 25%, 26 to 75%, and 91 to 100% or least disadvantaged
Accessibility/Remoteness Index of Australia^a^	Categorical	Major cities, inner regional, outer regional, remote and very remote

^a^These variables will be included in the models.

^b^This variable will be included in the subgroup analysis.

The Index of Relative Socio-economic Advantage and Disadvantage is a general socio-economic index derived by the Australian Bureau of Statistics, which includes 21 different measurements that reflect income, internet connection, occupation and education [29]. The Accessibility/Remoteness Index of Australia is a national measure of geographic remoteness and access to services for populated localities throughout Australia, based on road distance [30]. In our analyses, each of these indices will be determined according to the residential address of the mother at the time of their child’s birth.

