## Introduction

Conventional whole-cell pertussis vaccines (wP) were developed between the 1920s and 1940s [1], with subsequent widespread use in combination with diphtheria and tetanus toxoids as a three-dose primary schedule. The reactogenicity of these formulations is thought to be largely driven by the presence of endotoxin, and may manifest as self-limited injection site reactions, fever, irritability and other systemic symptoms [2,3].

The implementation of wP-based primary series in the past century successfully contributed to the near elimination of pertussis in countries like Australia which achieved high immunisation coverage [4]. From 1974, improved access to wP formulations through the Expanded Programme of Immunization has decreased vaccination inequalities in the developing world and the global burden of pertussis disease in children younger than 5 years old [5]. Nevertheless, geographical, social factors and weak health systems still drive vaccine inequity within low and middle income countries, substantially affecting the coverage of the first and third dose of pertussis vaccine primary series, and pertussis-related deaths [5,6]. Development of acellular subunit vaccines (aP) in the 1980s with substantially reduced endotoxin content and improved reactogenicity profile [7], prompted the switchover to aP primary immunisation in most high-income countries over the past 25 years.

In Australia, the transition from wP to exclusive use of aP vaccine formulations for the primary series occurred during the period of 1997 to 1999 [4]. During this period, existing batches of wP were used and fully depleted by community vaccine providers, before being replenished with batches of aP vaccine. This process occurred in a more-or-less stochastic fashion through the jurisdictional immunisation programs. Therefore, the receipt of wP or aP on the day of the first vaccination was not driven by the individual preference of carers or providers, but by which vaccine happened to be available at the primary care services and public immunisation clinics.

The period of switchover from wP to aP in Australia also overlapped with the change from the ninth to the tenth revision of the International Classification of Diseases (ICD) coding scheme. The first edition of ICD-10 AM (AM: Australian Modification) was introduced in New South Wales (NSW) in July 1998, and in Western Australia (WA) in July 1999 [8].

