#### Subgroup analysis

It is uncertain whether delaying the administration of a first dose of pertussis-containing vaccine affects the subsequent risk of developing atopic sensitisation or atopic diseases, with observational studies variously reporting a deleterious [34], beneficial [35–37], and no effects [38]. However, to the best of our knowledge, the relationship between atopic outcomes and age at vaccination has only been tested in recipients of the same type of vaccine, but not in a population vaccinated with a first dose of either, wP or aP. In order to explore possible modification of the effect of the immunisation with wP vs aP by age at vaccination, we will carry out subgroup analyses according to the age of the first dose of wP or aP (before or at 90 days of age, or after 90 days of age).

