### Pre-exposure domains

#### Bias due to confounding

Calendar date of birth, and state of birth are likely to be associated with one or more of the atopic disease outcomes of interest, either through a direct effect on the disease or through an effect on healthcare utilisation conditional upon disease. They are also known predictors of vaccination with wP versus aP during the transition to aP routine vaccination (Figs 3 and 4). Models will therefore be stratified by state of birth and adjusted for date of birth.

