**Fig 4 pone.0260388.g004:**
[figure not shown]
Direct acyclic graph after adjustment by confounders and baseline covariates. The blue node represents the exposure (wP or aP); orange and grey nodes: Perinatal, environmental and biological factors at birth/before the exposure that may influence the outcome of interest, but not the receipt of the study vaccines; brown nodes: Confounders of the association between the exposure and atopic asthma; yellow nodes: Adjusted variables; white node: Outcome of interest. Because the association between low birthweight and asthma is mainly driven by gestational age at delivery, birthweight is not depicted in this diagram [40]. C-section: Birth by caesarean. Data are available for all the nodes except for those in orange.

Age is associated with the risk of various atopic diseases, and while it is also associated with vaccination, it should not be associated with receipt of wP versus aP after controlling for date of birth; nonetheless, the Cox survival model intrinsically controls for any effect of age on the risk of outcomes [31].

Statistical models will be adjusted for socioeconomic index, accessibility or remoteness index, Aboriginal ethnicity (identified through a validated multi-stage median algorithm) [41], season of birth and birth order (i.e. the relative position of a child in relation to their siblings). These variables are plausibly associated with the atopic outcomes of interest, and might also be systematically different between children vaccinated with wP versus aP (Figs 3 and 4).

The prevalence of childhood asthma among Aboriginal and/or Torres Strait Islander people (hereafter respectfully referred as Aboriginal) has been measured by a number of surveys across different settings. According to the most recent National Aboriginal and Torres Strait Islander Health Survey (2018/2019), the prevalence of current and long-term asthma in children under 15 years old was similar for Aboriginal (11.5%; 95% CI 9.6% to 13.4%), and non-Aboriginal children (9.7%; 95% CI 8.5 to 10.9%) [42]. Older studies suggested Aboriginal children living in extremely remote WA may have a lower incidence of asthma across their life course (7.3%; 95% CI 5.3% to 9.7%) than those living in metropolitan Perth (30.5%; 95% CI 27.3% to 33.8%) [43].

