## Discussion

The proposed observational design will use administrative data to assess the hazard of hospital admission and emergency department presentation for allergic diseases in a birth cohort of children born in Australia during the transition from using wP to aP priming vaccine doses.

The limitations of this study have been described in the “Bias” section of this manuscript. Although more sophisticated techniques have been proposed in the causal inference literature for the selection of covariates and further statistical modelling [27,53], features inherent to the transition period, in particular the apparently untargeted manner in which wP versus aP vaccine doses were administered, may still enable us to treat these data as though from a randomised experiment after controlling for the two predictors of wP versus aP vaccination, namely the date and state of birth.

The aim of the proposed analysis plan is to assess for a possible causal effect of wP on prevention of asthma and other atopic diseases, although the potential for residual confounding and other biases means any protective association is unlikely to be sufficient to change policy. If support is provided, the results of this study could motivate and inform the implementation of randomised controlled trials in Australia, where wP has been phased out from the primary series of pertussis immunisation, and where the burden of atopic diseases in childhood is high [54].

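### Age at first dose is left out of the adjusted models, although on the protocol's own account it predicts wP versus aP once date and state of birth are known

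*Protocol article*

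**What the plan says.** Table 2 (Statistical analysis plan) sorts variables by footnote. Those with footnote a carry the note "These variables will be included in the models": sex, gestational age, method of delivery, Aboriginal status, season of birth, previous pregnancies, maternal smoking, the socio-economic index and the remoteness index. Age at the first dose has footnote b only: "This variable will be included in the subgroup analysis".

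The section on bias due to confounding adds calendar time and place: "Models will therefore be stratified by state of birth and adjusted for date of birth". It continues: "Statistical models will be adjusted for socioeconomic index, accessibility or remoteness index, Aboriginal ethnicity", followed by season of birth and birth order. Neither age at first dose nor date of first dose appears.

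On what decided the vaccine, the Introduction says that "the receipt of wP or aP on the day of the first vaccination was not driven by the individual preference of carers or providers". It attributes the choice instead to the stock that each clinic held that day, and describes wP stock being run down and then replaced by aP. The Exposure section excludes first doses given before 39 or after 111 days of age. The Discussion hopes to treat the data much like a randomised experiment "after controlling for the two predictors of wP versus aP vaccination, namely the date and state of birth".

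On the outcome side, the Subgroup analysis section says: "It is uncertain whether delaying the administration of a first dose of pertussis-containing vaccine affects the subsequent risk of developing atopic sensitisation". It expresses the same doubt about clinical atopic illness, and cites studies with harmful, beneficial and null results.

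**The concern.** If stock on the vaccination day decided the vaccine, the calendar variable that matters is the vaccination date. Birth date is only part of it; age at first dose is the rest. Among children with the same birth date and state, those vaccinated later met a later stock and were more likely to receive aP. At a fixed birth date the aP group therefore holds more late-vaccinated infants than the wP group.

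If late vaccination, or whatever causes it, is linked to asthma or atopic admissions beyond what the planned covariates capture, that link passes into the wP:aP hazard ratio. If late vaccination goes with higher risk, wP looks protective, which is the hypothesised direction. The Introduction describes the effect of interest as modest, so even a small distortion counts. The variable is already in hand.

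**Working it through.** The protocol article gives no figure to reproduce on this point: no transition curve, no distribution of age at first dose and no event count. The check has two parts.

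**1. Does age at first dose predict vaccine type, given birth date and state?** This follows from the text.

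- Date of first dose = date of birth + age at first dose.
- Allowed age is 39 to 111 days (Exposure), so dates for one birthday can span 111 − 39 = 72 days.
- The chance of aP rose with calendar date as wP was depleted (Introduction).
- Hence, for a fixed birth date and state during the transition, a later first dose means a higher chance of aP.

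**2. How large could the bias be?** All inputs here are assumptions:

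- the share given aP rises logistically with vaccination date, from 5% to 95% over T months;
- 15% of infants are vaccinated 35 days late and the rest on time;
- the hazard ratio (HR) for late versus on-time vaccination, left over after adjustment, is 0.8, 1.2 or 1.5;
- vaccine type has no true effect.

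The logit slope is 2 ln(19)/T per day. A 35-day delay multiplies the odds of aP by exp(35 × slope). For T = 6 months (182.6 days) the slope is 5.889/182.6 = 0.0323, and exp(35 × 0.03225) = 3.09.

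At each birth date the spurious ratio is

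HR(wP:aP) = [1 + P(late | wP)(h − 1)] / [1 + P(late | aP)(h − 1)],

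where h is the HR for late vaccination. Example for T = 6 months, at the birth date where an on-time child has a 50% chance of aP: a late child has 75.6%. Then P(late | aP) = 0.15 × 0.756 / (0.85 × 0.5 + 0.15 × 0.756) = 0.211, and P(late | wP) = 0.15 × 0.244 / (0.85 × 0.5 + 0.15 × 0.244) = 0.079. With h = 1.5 the ratio is 1.040/1.105 = 0.941. Averaging the log ratio over birth dates with weight p(1 − p), where p is the share given aP, yields:

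| Switch, 5% to 95% aP | Odds ratio for aP, 35 days later | h = 0.8 | h = 1.2 | h = 1.5 |
|---|---|---|---|---|
| 6 months | 3.09 | 1.029 | 0.973 | 0.937 |
| 12 months | 1.76 | 1.015 | 0.986 | 0.967 |
| 24 months | 1.33 | 1.007 | 0.993 | 0.983 |
| 36 months | 1.21 | 1.005 | 0.995 | 0.989 |

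**Cross-check by simulation, also on assumed inputs.** It used 329,831 children (the cohort size in the Abstract) born evenly over 1,095 days, a skewed age at first dose within 39 to 111 days (mean 68, SD 13), a logistic fall in wP with vaccination date, no true vaccine effect, and an outcome rate ratio of 0.8 to 1.25 per 30 days later dose. With a birth-date spline alone, the null rate ratio came out at 0.964 to 1.034 for a sharp switch (logistic scale 30 days) and 0.994 to 1.006 for a very gradual one (scale 200 days). With age at first dose added, it was 1.000 in every scenario.

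**The case against.** **The size is assumed and could be very small.** The Introduction dates the transition to 1997 to 1999, and no 6-month switch is documented. At 24 to 36 months the distortion is under 2%. Only an association that survives the planned covariates can leak. Those covariates include the socio-economic and remoteness indices, Aboriginal status, previous pregnancies and maternal smoking, so h = 1.5 is an upper-end input. This stands, and it limits the size.

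**The plan has safeguards.** Injury, trauma and poisoning codes serve as negative control outcomes for residual confounding, the age window is already restricted, and results are planned on either side of 90 days. These may reveal a problem, but none adjusts the primary hazard ratio. The 90-day split also leaves up to 51 days (39 to 90) and 20 days (91 to 111) of variation within strata.

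**The selection rule does not compel inclusion.** The rule for confounders admits common causes, proxies for unmeasured confounders and outcome predictors, measured before the first dose. Age at first dose is fixed at dosing, and its link to the outcome is uncertain. A reader might infer that the plan breaks its own rule; the documents do not support that. The omission is a judgement open to challenge. Equally, the reason for excluding post-exposure variables does not cover this one, since vaccine type does not cause it.

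**The protocol addresses age.** It says age should be unrelated to wP versus aP once date of birth is controlled, and that the Cox model handles age. This appears to mean attained age. Read as age at vaccination, it conflicts with the Introduction.

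**Table 2 may be incomplete.** Date of birth is adjusted for but not listed there, and the causal diagrams are not visible in the text at hand. But age at first dose is in the table and is expressly assigned to the subgroup analysis.

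**The subgroup analysis.** A reader might infer that effect modification will be judged by comparing two separate fits. The protocol does not say so and does not exclude an interaction term, so no criticism is made here.

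**Conclusion.** The point holds in a limited form. On the protocol's own account of how vaccines were allocated, age at first dose predicts wP versus aP given date and state of birth, so the Discussion's two-predictor statement is incomplete. The adjusted models omit the variable.

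Whether the omission biases the result depends on a residual link between age at first dose, or its causes, and the outcome. The protocol leaves that open. Under the assumed inputs a null hazard ratio shifts by about 3% to 6% for a 6-month switch and by under 2% for a switch of 24 months or longer. It does not shift if there is no residual link.

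A reader might conclude that the natural-experiment design fails. The documents do not support that. The Discussion sentence is hedged, the models adjust for more than the two named predictors, and the authors already say that residual confounding makes a policy change on these results alone unlikely. This is a gap worth closing because closing it is easy.

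**What to change.** Add age at first dose to the adjusted models, for example as a p-spline (which the plan already allows), alongside date of birth and stratification by state. In Table 2, give it footnote a as well as b. At minimum, pre-specify this as a sensitivity analysis of the primary model. Describe the term as age at first dose: smooth additive terms in birth date and age are not in general the same as a term in date of first dose.

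Amend the Discussion to name date of birth, age at first dose and state as predictors of vaccine type.

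The cost is one covariate already held in the immunisation register and a few words. The downside is a slight loss of precision if age at first dose proves unrelated to the outcome.

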### Statistical methods

#### Hospitalisations for asthma

We will compare rates of hospital admissions for asthma in children aged between 5 and 15 years old by means of unadjusted and adjusted Cox regression models for the time-to-first event [31], and Andersen-Gill models for recurrent events using robust standard errors to account for within-child dependence [32].

The person-time-at-risk is depicted in the following Lexis diagrams (Figs 1 and 2).

**Fig 1 pone.0260388.g001:**
[figure not shown]
Lexis diagram (before data cleaning). Legend: Person-time-at-risk experience of children born in WA or NSW between 1 January 1997 and 31 December 1999 before data cleaning.

**Fig 2 pone.0260388.g002:**
[figure not shown]
Lexis diagram (after data cleaning). Legend: Person-time-at-risk experience of children born in WA or NSW between 1 January 1997 and 31 December 1999 after data cleaning.

Each child will enter the cohort on the date of their fifth birthday and the analysis time will be based on days since entry to the cohort. For time-to-first event analyses, censoring will occur at the earliest of the following: first admission to hospital ICD-coded as ‘asthma,’ the date of death, the day before the 15^th^ birthday, or the end of follow-up (31 December 2013). The same rules will be applied to time-to-recurrent event analyses except there will not be censoring at the time of the first hospitalisation for the outcome of interest. Multivariable models will be stratified by jurisdiction of birth and, where required, non-linear elements (p-splines) will be incorporated.

#### Hospitalisations for other atopic outcomes

We will compare rates of admission for all-cause anaphylaxis, food anaphylaxis, venom, urticaria and atopic dermatitis by means of unadjusted and adjusted Cox regression models for the time-to-first event [31], and Andersen-Gill models for recurrent events using robust standard errors to account for within-child dependence [32]. For children born in WA, the cohort entry will be set at 4 months old, and vaccination status will be treated as a time-dependent covariate. For children born in NSW, the cohort entry will be set at 5 years old. Censoring rules will be applied as above.

#### Emergency department presentations

Emergency department presentations will be analysed using the same statistical approach specified for hospitalisations for asthma, with time zero defined in accordance with the data availability (i.e. the date of the fifth birthday for children born in WA, and the date of the eight birthday for those born in NSW).

All hypothesis tests will be two-sided at 0.05 significance level. All statistical analyses will be carried out in R [33], unless otherwise stated, using the Secured Unified Research Environment from the Sax Institute, NSW.

#### Sensitivity analyses

If numbers allow, we will run sensitivity analyses on the case definition of asthma by restricting the primary diagnosis to ‘predominantly allergic asthma’ (ICD 10-AM: J45.0) and ‘extrinsic asthma’ (ICD 9-CM: 493.0–493.1); we will also perform a sensitivity analysis on the case definition of all-cause urticaria, by only including admissions coded as ‘allergic urticaria’ (ICD 9-CM: 708.0 and ICD-10-AM: L50.0).

According to the extent of missing data, where applicable, sensitivity analyses will be run using suitable imputation techniques.

